## Discussion

Several studies have shown that TG level was associated with the development of organ failure in HTG-AP patients (6, 7, 10). However, few studies evaluated whether timely reduction of TG levels can impact the evolution of organ failure during the early phase of HTG-AP. A retrospective study found that patients reaching the target TG level of < 5.65 mmol/L faster were less likely to develop POF (*P* = 0.002) (10). However, considering the embedded bias of retrospective studies, prospective studies are needed to provide reliable data for future trials.

Despite the paucity of evidence, prompt reduction of triglycerides is commonly considered helpful (8, 25, 26). Given the role FFA may play in the pathophysiology of HTG-AP, insulin therapy seems promising, as it lowers TG level by reversing the stress-associated release of fatty acids from adipocytes, which can promote intracellular TG generation within adipocytes and fatty acid metabolism (27). For heparin, it stimulates the release of LPL from endothelial cells. However, its use remains controversial because the increase of serum LPL caused by heparin can decrease rapidly due to hepatic degradation, resulting in depletion in the LPL storage (13). Insulin/heparin treatment has been frequently used in the management of HTG-AP. However, its impact on TG reduction and clinical outcomes is unclear. A retrospective study conducted by Dhindsa et al. (28) showed a similar triglyceride-lowering effect between additional insulin infusion and conventional therapy. On the contrary, a meta-analysis reviewed three RCTs found intensive insulin therapy was associated with a shorter length of hospitalization and lower APACHE II score in SAP patients (29).

For blood purification, several studies assessed the effect of plasmapheresis on TG reduction and clinical outcomes. A systematic review involving eight studies found that it is effective in reducing TG level with a 69.6% decrease after treatment (14). Two studies reported a reduction of APACHE-II scores before and after plasmapheresis, while another retrospective study found plasmapheresis did not decrease morbidity or mortality (30–32). Based on the current evidence, HTG-AP is a category III, grade 2C indication for therapeutic plasma exchange in the American Society for Apheresis (ASFA) guidelines (15). Hemoperfusion (HP) is another blood purification modality that can absorb large pathogenic molecules from circulation by adsorbent materials installed in the HP cartridge. Hemofiltration is another choice, which was reported to be beneficial for AP patients (33, 34). However, there are no studies that have demonstrated the benefits of HP among HTG-AP patients by now. For other modalities, an RCT by He et al. (18) found that high-volume hemofiltration (HVHF) can lower TG levels more efficiently than insulin/heparin therapy but cannot improve clinical outcomes. A small pilot study enrolled 20 HTG-AP patients undergoing conventional treatment alone (the control group) or combined HVHF and HP treatment. The results showed a more significant reduction of TG level and improved clinical outcomes in the latter (35).

Taken together, there is no high-quality evidence demonstrating the clinical benefits of any specific TG-lowering therapy, and the primary choice of treatment varies significantly among different centers. In the 2021 Chinese guideline, TG lowering therapy, including fasting, medical treatment, and blood purification, are recommended when TG level is higher than 11.3 mmol/L. But the quality of evidence is moderate. Moreover, there are no clear recommendations regarding speficific TG-lowering therapy both in Chinese and international guidelines (23, 24, 36–38). The present study is designed to describe the current practice of TG-lowering therapy in HTG-AP and provide necessary data for future trials.

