## Abstract

**Background:** Acute pancreatitis (AP) is a potentially life-threatening inflammatory disease with multiple etiologies. The prevalence of hypertriglyceridemia-induced acute pancreatitis (HTG-AP) has been increasing in recent years. It is reported that early triglyceride (TG) levels were associated with the severity of the disease, and TG- lowering therapies, including medical treatment and blood purification, may impact the clinical outcomes. However, there is no consensus regarding the optimal TG-lowering therapy, and clinical practice varies greatly among different centers. Our objective is to evaluate the TG-lowering effects of different therapies and their impact on clinical outcomes in HTG-AP patients with worrisome features.

**Methods:** This is a multicenter, observational, prospective cohort study. A total of approximately 300 patients with HTG-AP with worrisome features are planned to be enrolled. The primary objective of the study is to evaluate the relationship between TG decline and the evolution of organ failure, and patients will be dichotomized depending on the rate of TG decline. The primary outcome is organ failure (OF) free days to 14 days after enrollment. Secondary outcomes include new-onset organ failure, new-onset multiple-organ failure (MOF), new-onset persistent organ failure (POF), new receipt of organ support, requirement of ICU admission, ICU free days to day 14, hospital free days to day 14, 60-day mortality, AP severity grade (Based on the Revised Atlanta Classification), and incidence of systemic and local complications. Generalized linear model (GLM), Fine and Gray competing risk regression, and propensity score matching will be used for statistical analysis.

**Discussion:** Results of this study will reveal the current practice of TG-lowering therapy in HTG-AP and provide necessary data for future trials.

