### Study Population

Recruitment started on November 1st, 2020, and is scheduled to end on October 31st, 2022. This study is planned to recruit patients admitted to 30–40 hospitals across China. All adult patients presenting with early HTG-AP with worrisome features would be consecutively enrolled. The definition for HTG-AP with worrisome features is indicated as below.

All adult patients with AP admitted to the participating centers will be assessed for eligibility after admission (Figure 1). The inclusion and exclusion criteria are as follows:

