### Sample Size Justification

Based on the feasibility and patient flow of the participating sites, a sample size of 300 patients was expected, with an average of 15 patients per month within 2 years. Considering an estimated 20% rate of incomplete data or losses of follow-up, our expected sample size (240 patients) would provide 87% to detect a 2-days (SD: 5) or 82.5% for 1.5-days (SD: 4) improvement of organ failure free days between patients achieve target TG and those not.

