### Statistical Analysis

Continuous normally distributed data were reported as means with SDs. Skewed continuous data were reported as medians and interquartile ranges (IQRs). Categorical data will be summarized by counts and percentages. The intergroup difference will be compared by Student's *t*-test or Wilcoxon rank-sum test for continuous variable depending on their normality and chi-square test for categorical data.

To evaluate the association between TG decline and OF free days, the study patients will be dichotomized depending on whether the TG level reaches 5.65 mmol/L on Day 3 (the day of enrollment is labeled Day 1, the next day labeled Day 2, and the following day Day 3). For the primary outcome comparison, Wilcoxon rank-sum test will be employed. However, since OF could be evaluated with a time-to-event analysis censored at 14 days to account for the mortality as a competing event, Fine and Gray competing risk regression is used to assess the group difference as a supportive analysis.

For the association between different TG lowering therapy and OF free days, we considered the possibility that baseline characteristics, which were expected to be prognostic for OF, differ according to the choice of TG lowering therapies (i.e., blood purification treatment and medical treatment). A propensity score matching will be further used to compensate for the intergroup unbalance.

For secondary outcomes, a multivariate analysis generalized linear model (GLM) model will be performed to identify its association with TG decline and TG-lowering therapy with proper link and distribution function. The variable included in the model will be age, sex, TG level at enrollment, and other baseline variables that have significant differences between groups.

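### The primary Wilcoxon comparison pools 30–40 hospitals with no allowance for centre, although the article says therapy choice varies by centre; centre can therefore confound it

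*Protocol article*

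**What the plan says.** The Study Population section states: "This study is planned to recruit patients admitted to 30–40 hospitals across China". The article says in two places that management depends on where a patient is treated: the Abstract has "clinical practice varies greatly among different centers" and the Discussion has "the primary choice of treatment varies significantly among different centers". Treatment is left to the treating physician (text under Exclusion Criteria).

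The Statistical Analysis section fixes four methods:

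- **Primary comparison** (TG of 5.65 mmol/L reached on Day 3 or not): Wilcoxon rank-sum test, with no strata or covariates.
- **Supportive analysis:** Fine and Gray competing risk regression, with no covariates or clustering named.
- **Therapy comparison:** propensity score matching on baseline characteristics that are not listed.
- **Secondary outcomes:** a generalized linear model, for which "The variable included in the model will be age, sex, TG level at enrollment", plus baseline variables that differ significantly between groups.

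The Sample Size Justification allows for 20% incomplete data or loss to follow-up, and says that the remaining 240 patients "would provide 87% to detect a 2-days (SD: 5"). It makes no allowance for clustering.

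**The concern.** The article supplies a chain from centre to the primary exposure. Centres differ in therapy, and therapies differ in TG lowering: the Background describes plasmapheresis as clearing TG quickly and cites a randomized trial in which high-volume hemofiltration lowered TG more than medical therapy, and the Discussion cites a review with a 69.6% fall after plasmapheresis. Reaching the target on Day 3 may therefore depend partly on the hospital.

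Two problems can follow. If hospitals that reach the target more often also differ in case mix, referral or supportive care, an unadjusted comparison attributes those differences to TG decline. Even without that, patients from one hospital tend to resemble each other, and the rank-sum test assumes that they do not. The results are meant to inform future trials, so a centre effect mistaken for a TG effect would carry forward into their design.

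**Working it through.** **Inputs.** From Study Population: 30–40 centres. From Sample Size Justification: 300 × 0.8 = 240 evaluable patients, so m = 240/40 = 6 to 240/30 = 8 per centre on average; effects of 2 days (SD 5) and 1.5 days (SD 4), or 0.40 and 0.375 SD. The significance level and group split are not stated; I assume two-sided 0.05 and 120 per group. The article gives no ICC. I assume 0.05–0.10 for the outcome (ρY) and, for the exposure, a centre effect on the log-odds of reaching the target with SD s = 1–2 at 50% prevalence. On the observed scale that is an exposure ICC of ρX = Var(p)/0.25 = 0.17–0.39.

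**1. The stated power.** The noncentrality is 0.40 × √60 = 3.10 and 0.375 × √60 = 2.90. The two-sample t power is 87.0% and 82.5%, which matches the article. The stated figures are therefore those of 240 independent patients split equally.

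**2. Clustering alone, effect on power.** Design effect = 1 + (m − 1) × ρY × ρX, and 120 per group is divided by it.

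- ρY 0.05: from 1 + 5 × 0.05 × 0.17 = 1.04 to 1 + 7 × 0.05 × 0.39 = 1.14. Power for 2 days is 82–86%.
- ρY 0.10: from 1 + 5 × 0.10 × 0.17 = 1.09 to 1 + 7 × 0.10 × 0.39 = 1.28. Power for 2 days is 78–84%.
- For 1.5 days (SD 4), the two ranges together give about 73–81% against 82.5%.

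**3. Type I error of the nominal 5% Wilcoxon test.** I simulated a normal outcome with no exposure effect, 30 centres of 8 or 40 centres of 6, and 4,000 runs per setting. Here r is the correlation between a centre's effect on exposure and its effect on outcome. Monte Carlo standard error is about 0.3–0.7 points.

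| r (assumed) | ρY = 0.05 | ρY = 0.10 |
|---|---|---|
| 0 | 5.2–6.7% | 5.8–8.1% |
| 0.3 | 6.8–11.4% | 8.9–16.6% |
| 0.5 | 10.4–18.9% | 16.5–32.6% |

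**4. Spurious difference.** Under this model the expected difference with no true effect is SD × √ρY × r × s × (1 − ρX). The last two factors give 1 × 0.83 = 0.83 for s = 1 and 2 × 0.61 = 1.21 for s = 2.

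- SD 5, smallest: 5 × 0.224 × 0.3 × 0.83 = 0.28 day.
- SD 5, largest: 5 × 0.316 × 0.5 × 1.21 = 0.96 day.
- SD 4: 0.22 to 0.77 day.

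The real outcome is bounded at 0–14 days with a mass at zero, so the normal model gives orders of magnitude only.

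**The case against.** Four objections deserve weight.

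**Confounding is not shown.** A reader might infer that centre does confound the comparison, and in a known direction. The documents do not support that. The two statements about varying practice occur in summaries of the field, not in a description of the study's own sites. Physician discretion allows variation within a hospital. The Discussion also cites a retrospective study in which adding insulin infusion lowered TG about as much as conventional therapy, so different therapy need not mean a different Day 3 TG. Nothing in the article links centre to organ-failure-free days. This stands, and the claim is therefore that centre can confound.

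**Silence in a condensed article.** A reader might infer that centre is excluded from every analysis. The propensity covariates are unlisted, the generalized linear model list is open-ended and the Fine and Gray covariates are not given, so a fuller plan could include centre in all three. This also stands: there the gap is one of specification. It does not reach the primary test. A plain rank-sum test is a stated choice, and it cannot adjust for anything.

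**Larger power losses.** Setting ρX = 1 gives design effects of 1.25–1.35 (ρY 0.05) and 1.5–1.7 (ρY 0.10), and power of 76–79% and 66–71%. Those figures require the hospital alone to decide who reaches the target, which the article does not say.

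**Centre is only one unadjusted factor.** True: the primary test adjusts for nothing. But centre is the one source of treatment variation that the article names twice, and it can be handled cheaply. Every secondary endpoint is declared hypothesis generating, which lowers the stakes there but not for the primary outcome.

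**Conclusion.** The point holds for the primary comparison: it is fixed in a form that treats patients from 30–40 hospitals as independent and cannot account for centre, while the article's own text makes centre a plausible determinant of the exposure. Clustering by itself matters little at 6–8 patients per centre: power of about 78–86% instead of 87%, and type I error of about 5–8%. The main risk is confounding, which could produce a false difference of up to about half the 1.5–2 day target and a false-positive rate from about 7% to just over 30%. These sizes rest on assumed ICCs and an assumed correlation of 0.3–0.5 between centre effects. If that correlation is near zero, only the modest clustering effect remains. The plan should be changed, but it is not shown to give a biased answer.

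**What to change.** - **Primary outcome:** add a model of organ-failure-free days with target reached as the exposure and a random intercept for centre, or replace the plain test by a centre-stratified van Elteren test with small centres pooled by a rule set in advance. Report the effect with and without centre. With small centres a random intercept removes between-centre confounding only in part. Adding each centre's proportion reaching the target as a covariate separates the within-centre from the between-centre association.
- **Fine and Gray and generalized linear models:** use centre-clustered standard errors.
- **Propensity score:** state that centre, or the centre's blood-purification rate, enters the score.

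Random effects or pooling suit these data better than fixed effects for 30–40 centres of 6–8 patients. The change is to analysis wording only. Data are entered by each centre's own investigators, so centre should be identifiable, and no further patients or measurements are needed. The price is slightly wider intervals and some loss of information from centres with few patients. In a stratified test, a centre whose patients all fall in one group contributes nothing.

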## Ethics Statement

The PERFORM study was approved by the Ethics Committee of Jinling Hospital Nanjing University (No. 2020NZKY-016-01) prior to recruitment. All the participating sites are required to obtain local ethics approval before the commencement of recruitment. The participants will provide their written informed consent to participate in this study.

